### Data management

Data are collected on patient demography, medical history, concomitant therapy, duration of CRRT, and dose and duration of esmolol. Vital and health status are assessed at the time of weaning from ECMO, discharged from ICU and hospital, unplanned hospital readmission, EQ-5D scores, and SAEs, during follow-up via telephone, face-to-face, or remote medical consultation over 365 days. To improve monitoring adherence, the clinician will take time to explain about the need for follow-up surveillance and encourage the participants to undergo routine examinations. Data are entered into a secure password-protected electronic data capture system and checked for quality by research staff. All queries are listed for content and raised and resolved dates. All study records required by the coordinating center at the Heart Health Research Center (HHRC) and applicable regulatory bodies are maintained for 15 years. The confidentiality of all participant information must be protected at the clinical sites and the coordinating center. Paper records and computer files must be appropriately safeguarded from unauthorized access.

### Sample size

Sample size calculation is performed using the software PASS 15.0.5 based on the following assumption: a 70% 30-day mortality in the control group and a 20% relative risk reduction for each intervention (early CRRT and beta-blocker). The estimate of the intervention’s effect size was based on clinical expertise and the clinical significance of an intervention, no loss of follow-up or crossover, and 5% type I error and 20% type II error. We assume no interaction between interventions, as the overlap of the time of interventions would be limited and no carry-on effect expected. A total of 496 patients (248 per group) are required for each arm.

To achieve adequate participant enrolment to reach the target sample size, the study will be conducted at 10 high-volume centers in China. A smartphone application has been developed to facilitate randomization at the emergency room.

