## Methods

### Study design (Fig. 1)

ELITE is a prospective, multi-center, open-label, randomized controlled trial, with a 2 × 2 partial factorial design to evaluate whether early CRRT support and beta-blockade will reduce 30-day mortality in a broad range of ECMO patients admitted to hospitals in China from July 2018. In arm A, patients are randomized to early CRRT within 24 h of initiation of ECMO or to control, regardless of whether there is a conventional indication, or to the control where patients only receive CRRT according to a conventional indication. In arm B, patients are randomized to the intravenous esmolol group or usual care. The trial design and protocol adhere to the Recommendations for Interventional Trials (SPIRIT) criteria [19] (Table 1) and checklist in Table 5 in Appendix. The study is planned to enroll patients from 10 centers in China (see Table 5 in Appendix for the hospital list).

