### Eligibility

The broad inclusion criteria are used for both arms, whereby adult patients who have received ECMO for any reason within 24 h and 7 days, for arms A and arm B, respectively, are eligible (Tables 2 and 3). Patients are excluded from arms A and B if they had a definite indication or contraindication to either CRRT or beta-blockers, respectively. As ECMO is often initiated by a specialist team to rescue and transfer patients to larger hospitals in China, a timeframe of 24 h after ECMO implantation was used for early CRRT in arm A, while a relatively stable hemodynamic status (dopamine/dobutamine < 5 μg/kg/min, with no administration of adrenaline or norepinephrine) and within 7 days after initiation of ECMO was required for eligibility into arm B. Identification of potentially eligible patients is the responsibility of the ECMO team in participating centers. After ECMO implantation or when the patient is transferred to the participating center, eligibility for study arm A will be assessed. Prior to 7 days after ECMO implantation, when patients are stable on ECMO, eligibility for study arm B will be assessed.

**Table 2 Tab2:** Inclusion and exclusion criteria for study A

Inclusion criteria	
Patients receiving VA-ECMO for any reason within 24 h	
Provision of informed consent	
Exclusion criteria	
Age < 18 years	
Receiving ECMO bridging to heart transplantation	
With convention indication of CRRT: AKI prior to enrollment caused by any reason, at least one of the following criteria is met:	
Severe hyperkalemia (> 6.5 mmol/L)	
Metabolic acidosis (pH < 7.2)	
Pulmonary edema	
Blood urea nitrogen level > 112 mg/dL	
Oliguria (urine output < 200 mL/12 h) for more than 72 h	
CKD, with estimated GFR<30 mL/min	
Have already initiated CRRT	
Active hemorrhage/thrombotic thrombocytopenic purpura	
Receiving ECMO again during hospitalization or respiratory failure has already initiated VV-ECMO or extracorporeal carbon dioxide removal device before the initiation of VA-ECMO of this time	

*AKI* chronic kidney disease, *CKD* chronic kidney disease, *CRRT* continuous renal replacement therapy, *ECMO* extracorporeal membrane oxygenation, *GFR* glomerular filtration rate, *VA-ECMO* veno-arterial extracorporeal membrane oxygenation, *VV-ECMO* veno-venous extracorporeal membrane oxygenation

**Table 3 Tab3:** Inclusion and exclusion criteria for study B

Inclusion criteria	
Patients receiving VA-ECMO for any reason	

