### Interventions

Patients assigned to early CRRT should have it applied concurrently with ECMO treatment and continued for ≥ 12 h. Those assigned to standard therapy should receive CRRT according to the 2012 Kidney Disease: Improving Global Outcomes (KDIGO) Clinical Practice Guideline for AKI stage 3 and have at least one of the following criteria met: severe hyperkalemia (> 6.5 mmol/L), metabolic acidosis (pH < 7.2), pulmonary edema unresponsive to diuretic therapy, requiring oxygen flow rate of > 5L/min to maintain an oxygen saturation (SpO_2_) of > 95% or requiring a forced inspired oxygen concentration (FiO_2_) of > 50% on ventilation, blood urea nitrogen level > 112 mg/dL, or oliguria (urine output < 200 mL per 12 h) for > 72 h. CRRT can be initiated or discontinued according to the attending clinician’s decision in managing the patient.

In arm B, patients assigned to the intervention group are to receive a continuous infusion of esmolol on top of conventional management, commencing at 25 mg/h and increasing by 25 mg/h every 20 min until the heart rate is reduced to 75 ± 5 bpm or an upper dose limit of 2000 mg/h is reached. Esmolol infusion should be continued to maintain the heart rate threshold or according to the clinician’s discretion until discharge from the intensive care unit (ICU) (or death, if sooner). Oral beta-blockers should be introduced before esmolol is withdrawn. Esmolol can be transiently stopped or completely withdrawn should a patient develops third-degree atrial-ventricular block, bradycardia (< 60 bpm), extreme left ventricular systolic dysfunction, aortic valve dysfunction, or severe cardiogenic pulmonary edema. Patients in the control group will not receive any type of beta-blockers, unless the clinician considers there is a strong indication. Concomitant diseases will be treated following the current guidelines.

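### On the plan's own inputs, 496 patients give about 90% power, not the stated 80%, which needs about 372

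*Protocol article*

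**What the plan says.** The Sample size section assumes 70% mortality at 30 days in the control group and a 20% relative reduction for each intervention, with "no loss of follow-up or crossover" and "5% type I error and 20% type II error". It concludes that 496 patients, 248 per group, are needed for each of the two comparisons. The Abstract repeats 496 with 80% power. Randomization is 1:1, and Statistical analysis makes all tests two-sided and names the log-rank test for the primary outcome, analysed by intention to treat.

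On control treatment, Study design describes "the control where patients only receive CRRT according to a conventional indication". Interventions gives the detailed rule, beginning "Those assigned to standard therapy should receive CRRT according to the 2012 Kidney Disease": AKI stage 3 plus at least one listed criterion. The next sentence starts "CRRT can be initiated or discontinued according to the attending" and leaves the decision to the clinician, without naming a group or referring back to the criteria.

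**The concern.** A sample size, its inputs and its power should agree. Here they do not: 496 is clearly more than 80% power needs on the stated inputs. A reader who takes the statement at face value believes that the trial has no power in reserve, when on its own assumptions it has about ten percentage points.

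This matters in two ways. First, Trial status reports 89 patients enrolled in study A and a feasibility review by the Steering Committee at the end of 2022. That review should know which power the target of 496 corresponds to. Second, the plan sets loss and crossover to zero in an open-label trial analysed by intention to treat. The unstated reserve is what would absorb modest departures from that assumption, and a reader cannot see that it exists.

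**Working it through.** **Inputs.** Control mortality p1 = 0.70; intervention mortality p2 = 0.70 × 0.80 = 0.56; difference 0.14; loss and crossover 0 (Sample size). Two-sided 5%, z = 1.960 (Statistical analysis). Allocation 1:1 (Randomization).

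**Formula (pooled two-proportion).** With p̄ = 0.63:

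n per group = [1.960 × √(2 × 0.63 × 0.37) + z_β × √(0.70 × 0.30 + 0.56 × 0.44)]² / 0.14²

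The two roots are √0.4662 = 0.6828 and √0.4564 = 0.6756.

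- 80% power, z_β = 0.8416: (1.3382 + 0.5686)² / 0.0196 = 185.5, so 186 per group, 372 in total.
- 90% power, z_β = 1.2816: (1.3382 + 0.8658)² / 0.0196 = 247.8, so 248 per group, **496 in total**. This reproduces the plan's figure.

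**Power at 248 per group.** z_β = (0.14 × √248 − 1.3382) / 0.6756 = 1.283, so power is 0.900. At 186 per group it is 0.801.

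**Log-rank approximation (the named primary test).** Under proportional hazards, HR = ln(0.44)/ln(0.30) = 0.682. Expected deaths = 248 × (0.70 + 0.56) = 312.5. z_β = (√312.5 / 2) × |ln 0.682| − 1.960 = 1.424, so power is 0.923. The Freedman version gives 0.917. For 80% power, 215 to 220 deaths are needed, or about 342 to 350 patients.

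**Other routes to 496 at 80% power, total patients:**

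| Variant | Total |
|---|---|
| Unpooled | 366 |
| Pooled | 372 |
| Continuity-corrected | 400 |
| One-sided (without / with continuity correction) | 294 / 320 |
| Alpha 2.5% for two comparisons (without / with continuity correction) | 450 / 478 |
| HR of 0.80 instead of a 20% risk reduction | about 957 to 1,010 |

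None gives 496.

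**How far the reserve goes (illustrative).** Suppose a share x of controls crosses over to early CRRT and gains the full average benefit. Control mortality is then 0.70 − 0.14x against 0.56.

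| x | Two-proportion power | Log-rank power |
|---|---|---|
| 0 | 0.900 | 0.923 |
| 5% | 0.867 | 0.893 |
| 10% | 0.827 | 0.857 |
| Power reaches 0.80 at | x = 13.0% | x = 16.3% |

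In patients, the limits are 0.130 × 248 = 32 and 0.163 × 248 = 40 controls. They move with the assumptions. By the two-proportion test, 5% loss to follow-up lowers 13.0% to 10.8%, and 10% loss lowers it to 8.5%. If 5% of the early group never receives CRRT, the limit is 8.3%. With a continuity correction it is about 10%. If crossed-over controls gain only half the benefit, it rises to 26%. The documents give none of these rates; all are assumptions.

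**The case against.** **The error is harmless, because the trial is larger than it needs to be.** This stands as to direction: the stated 80% is not shown to fail. It does not make the statement right.

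**The 496 may contain an allowance that the article leaves out.** For example, 372 / 0.75 = 496, so a 25% inflation of the 80% size lands on the same number. The document rules this reading out as written, since it sets both loss and crossover to zero. How 496 arose cannot be settled from the article, but the inputs, power and size it prints together are inconsistent.

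**A stronger reading of the discretion sentence.** A reader might infer that Interventions allows control patients to start CRRT outside the criteria, contradicting both Study design and the zero-crossover assumption, so that power is at risk. The documents do not support that. The sentence directly follows the specific control rule, Study design says controls get CRRT only on a conventional indication, and the ordinary reading is management within the assigned strategy. Zero crossover is a planning assumption, not a rule of conduct. No crossover rate is given, patients already indicated for or already on CRRT are excluded at entry ("Have already initiated CRRT"), and Monitoring has protocol deviations reported to the DMC. What remains is unclear wording. For beta-blockers the same section does state its exception ("Patients in the control group will not receive any type of beta-blockers, unless the clinician considers there is a strong indication"), whereas for CRRT it does not say how far discretion reaches.

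**The 13% could be read as a guarantee.** It is not one. It depends on the test, zero loss, full adherence in the early group and full average benefit in those who cross over.

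**Conclusion.** The power statement is wrong as written. On the stated inputs, two-sided and 1:1, 496 is the 90%-power size: power is 0.900 by the two-proportion test and about 0.92 by log-rank approximation. The stated 80% needs about 372 patients by the pooled formula, and 342 to 400 across the standard two-sided variants for 70% against 56%. The result assumes, as the plan does, 70% control mortality, a 20% relative reduction, no loss and no crossover; the log-rank figures also assume proportional hazards. The misstatement is conservative and does not show an underpowered trial. The discretion sentence is a minor wording matter with no demonstrated effect on power.

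**What to change.** In the Abstract and in Sample size, restate that 496 patients (248 per group) give about 90% power, i.e. 10% type II error, for 70% against 56% mortality at two-sided 5% with no loss to follow-up or crossover. Sample size and analysis stay as they are.

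If tolerated control crossover is mentioned, give it as an illustration (about 13% by two-proportion test, about 16% by log-rank) and state its conditions: zero loss, full early-group adherence, and full average benefit in crossed-over controls.

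Optionally, in Interventions, say that starting and stopping at the clinician's decision applies within the assigned strategy. Keep the control rule in full: KDIGO stage 3 AKI and at least one listed criterion. A replacement that asked only for a listed criterion would loosen the control strategy.

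The cost is one corrected statement in two places and, if taken up, one clarified sentence.

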**Methods:**

A 2 × 2 partial factorial randomized controlled trial in eligible ECMO patients without a clear indication or contraindication to either intervention is centrally randomly assigned to (A) early or conventional-indicated CRRT and/or (B) beta-blocker or usual care. The primary outcome is all-cause mortality at 30 days for both arms. A total of 496 participants provides 80% power to determine a 20% risk reduction in mortality at 30 days with 5% type I error.

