### Trial status

There have been 89 patients enrolled at 10 hospitals in study A, and the enrollment is still ongoing. However, study B was stopped in August 2019 in the absence of any patients being enrolled. Although we aimed to test the hypothesis that beta-blockers would protect the myocardium in ECMO patients, we found this too challenging to undertake as these patients have low BP, which is a contraindication to such treatment and raised concerns of harm among investigators. Moreover, the short time window for enrollment was another barrier to recruitment, and by the time a patient is stable and without vasopressors, it is near the time to wean them off ECMO. Consequently, we decided to close recruitment into arm B. During the COVID pandemic, patient enrollment has become more challenging. A review of the feasibility of the trial will be made by the Steering Committee at the end of 2022.

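### Under the stated assumptions 496 patients give 90% power, not the stated 80%; 80% power needs about 372

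*Protocol article*

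**What the plan says.** The Sample size section of the protocol article starts from "a 70% 30-day mortality in the control group" and a 20% relative risk reduction for each intervention. It adds "no loss of follow-up or crossover, and 5% type I error and 20% type II error". It assumes no interaction between the two factors, and from these inputs concludes: "A total of 496 patients (248 per group) are required for each arm".

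The Methods paragraph of the abstract makes the same pairing: "A total of 496 participants provides 80% power to determine a 20% risk reduction in mortality at 30 days".

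Other sections supply the rest of the inputs. Randomization gives 1:1 allocation. Statistical analysis makes all tests two-sided at 5% and names a log-rank test for the primary outcome. Monitoring plans no interim efficacy analysis, so no alpha is spent early.

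Trial status reports 89 patients enrolled in study A and says: "A review of the feasibility of the trial will be made by the Steering Committee at the end of 2022".

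**The concern.** The article fixes every input of a standard two-group calculation, so the sample size should be reproducible. It is not: 248 per group is well above what these inputs need for 80% power, and it equals the answer for 90% power. Either the type II error is misstated, or the number contains an allowance that the same paragraph says was not made.

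The practical stake is the feasibility review. Anyone who takes the text at face value will believe that falling short of 496 drops the trial below 80% power. Under the stated assumptions that happens only below about 372. Conversely, a trial that reaches 496 has more power than its authors report.

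**Working it through.** **Inputs**

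- Control mortality p1 = 0.70 (Sample size).
- Intervention mortality p2 = 0.70 × (1 − 0.20) = 0.56 (Sample size).
- Two-sided alpha 0.05, z = 1.960 (Sample size; Statistical analysis).
- Type II error 20%, z = 0.842 (Sample size; abstract).
- Allocation 1:1 (Randomization).
- No inflation for loss, crossover, interaction or interim looks (Sample size; Monitoring).

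**Formula** (two proportions, pooled variance under the null)

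n per group = [z(α/2)·√(2·p̄·(1 − p̄)) + z(power)·√(p1·(1 − p1) + p2·(1 − p2))]² / (p1 − p2)²

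Here p̄ = (0.70 + 0.56)/2 = 0.63 and (p1 − p2)² = 0.14² = 0.0196.

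- First term: 1.960 × √(2 × 0.63 × 0.37) = 1.960 × 0.6828 = 1.3382.
- Second square root: √(0.21 + 0.2464) = 0.6756.

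**Attempt to reproduce 248 per group**

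- 80% power: (1.3382 + 0.842 × 0.6756)² / 0.0196 = (1.9068)² / 0.0196 = 185.5, so 186 per group, 372 in total.
- 85% power: 212.0 per group.
- 90% power: (1.3382 + 1.282 × 0.6756)² / 0.0196 = (2.2040)² / 0.0196 = 247.8, so **248 per group, 496 in total**.

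The stated figure is reproduced at 10% type II error, not at the stated 20%.

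**Power at the stated size**

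- 248 per group: z = (0.14 × √248 − 1.3382) / 0.6756 = (2.2047 − 1.3382) / 0.6756 = 1.283, so power is 90.0%.
- 186 per group: power is 80.1%.
- At 80% power, 496 patients would detect a 17.2% relative reduction (70% to 58.0%).

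**Does another method give 496 at 80% power?**

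| Method at 80% power (two-sided 5% unless stated) | Total N |
|---|---|
| Pooled two-proportion | 372 |
| Unpooled two-proportion | 366 |
| Arcsine | 372 |
| Continuity-corrected | 400 |
| Fisher exact | about 398 to 400 |
| Log-rank, Schoenfeld (hazard ratio ln 0.44 / ln 0.30 = 0.682; 63% events) | 342 |
| Log-rank, Freedman (same hazard ratio) | 350 |
| One-sided 5%, pooled | 294 |
| Two-sided 2.5%, pooled / continuity-corrected | 450 / 478 |
| 20-point absolute difference (70% vs 50%) | 186 |
| Log-rank, taking 0.80 as the hazard ratio | 958 to 965 |

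None gives 496. The methods that match the stated inputs run from 342 to 400. At 496 patients, power is 88.3% by Fisher exact test and 92.3% by log-rank with hazard ratio 0.682, so about 90% holds whichever test is used.

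**A hidden allowance**

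186 / 0.75 = 248, so an allowance for 25% attrition (an increase of one third) also reaches the stated figure. The Sample size section excludes it by assuming no loss and no crossover.

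**Size of the gap:** 496 − 372 = 124 patients; 124 / 372 = 33%.

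**Power if recruitment ends early** (pooled formula, 70% vs 56%): 27% at 89 patients, 54% at 200 and 71% at 300.

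**The case against.** The mismatch itself cannot be argued away, but several points limit what follows from it.

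- **The error is conservative.** If the design intended 90% power, the target, design and analysis all stand and only the wording is wrong. The exact match at 90% makes that plausible, although the article cannot settle it. This stands.
- **372 is not a safe replacement target.** It holds for the two-proportion formula at exactly 70% control mortality, while the Introduction gives 60 to 75% for this population. With the same 20% relative reduction, 80% power needs 450 patients at 65% control mortality and 540 at 60%. At 60%, 496 patients give only 76.6% power and 372 give 64.2%; 496 falls to 80% at about 62.3%. The surplus is therefore useful margin, and lowering the target mid-trial would be a design decision, not an edit. This also stands.
- **The planned primary test is log-rank.** The figure of 372 is specific to the two-proportion formula. True, but the log-rank answer is smaller (342), so the gap widens.
- **The correction may not change the feasibility verdict.** If the 89 patients had accrued by mid-2022 (an assumption), the rate is about 22 a year. Then 124 patients are 5 to 6 years of recruitment, but reaching 372 would still take 283 more patients, about 13 years. The article also gives no criteria for the review. This is fair. It reduces the practical consequence but does not make the stated power correct.

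**Conclusion.** The point holds. The stated sample size and the stated power contradict each other, in the Sample size section and again in the abstract. On the article's own inputs (70% vs 56%, two-sided 5%, 1:1, no attrition or crossover), 496 patients give 90.0% power, and 80% power needs 372, with 342 to 400 across reasonable tests. The size stated for 80% power is too large by 124 patients, or 33%, on the two-proportion formula. The trial is not underpowered at 496 if 70% control mortality is right. What is wrong is the power statement, or else the statement that no allowance was made. The article does not show which.

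**What to change.** Establish from the original calculation which figure was intended, then correct the Sample size section and the abstract in the same way:

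1. If 90% power was intended, keep 496 and state 90% power with 10% type II error. This fits the number exactly and leaves the target unchanged.
2. If 80% power was intended and 496 includes an allowance for about 25% attrition or an equivalent dilution, state it and remove the assumption of no loss and no crossover.
3. If 80% power was intended with no allowance, the figure is 372 (186 per group). Adopting it as the target would be a design change and should be justified against control mortality of 60 to 75%.

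Give the Steering Committee both sizes (372 for 80%, 496 for 90%), the power at attainable sizes, and the sensitivity to control mortality.

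Options 1 and 2 cost a corrected sentence in each of two places and no extra patients. Option 3 lowers the requirement but gives up the margin against a lower control mortality.
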